## Statistical methods

Statistical analyses will be carried out using MATLAB 2020b, R version 3.5.2, and Statistica software.

The risk of error will be set at 5%, and two-tailed tests will be used.

Missing data will be replaced by the mean of the variable in the sample for the group under consideration (POTs or active control).

First, the number of participants will be described in a flow chart (included and excluded subjects, reasons for exclusion, subjects included, or not, in the analysis and reasons for exclusion). A descriptive analysis will then be run on all of the variables collected, and for each of the two groups (POTs *vs.* active control). Qualitative variables will be described using frequencies and percentages, while quantitative variables will be described using mean and standard deviation, or medians and interquartile ranges.

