### End-of-study visit

Participant follow-up will end either: (*i*) on the day following the last session of the POTs or the active control intervention; or (*ii*) the day they leave the course (for whatever reason), if this occurs before the end of the intervention (POTs or active control).

A posturography measurement will be performed by the military medic, or one of his or her assistants, and the participant will complete questionnaires measuring postural awareness (the Postural Awareness Scale) and perceived stress (Cohen’s Perceived Stress). Finally, a 4 ml saliva sample will be collected.

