# STATISTICAL ASPECTS

## Calculating the number of subjects required

To date, there are no data in the literature on the effectiveness of POTs in preventing sports-related injuries. However, discussions with military unit managers and medical officers suggest that a reduction in the injury rate of around 15% would be clinically relevant. Preliminary epidemiological data from the various units indicates that the rate of fall injuries is around 50%.

To determine the sample size required to observe a significant difference in rates between the two groups, we used the following parameters:

- statistical test: two-tailed
- fall rate in the active control group: 50%
- fall rate in the POTs group: 35%
- statistical significance = 0.05
- power = 0.80

Taking into account potential drop-outs (estimated at 10%), the sample should consist of 200 participants per group, for a total of 400 participants over the two years of the study.

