**Analysis of secondary objectives**

For the first secondary objective, the effect of the POTs intervention on postural awareness will be evaluated by comparing the following for the POTs group: (*i*) scores on the Postural Awareness Scale at the six measurement times (repeated measures ANOVA), and (*ii*) posturography measurements pre- and post-intervention (paired samples comparison of means).

For the second secondary objective, the effect of the POTs intervention on the psychobiological stress response will be evaluated by comparing the following measures for the POTs group at all six measurement times: (*i*) scores on Cohen’s Perceived Stress Questionnaire (repeated measures ANOVA), and (*ii*) biological stress variables (paired samples comparison of means).

For the third secondary objective, machine learning will be used to evaluate the accuracy of the predictive model of the risk of fall injury using the following calculation:

|  | $\text{Accuracy=}\frac{\text{True }\text{Fall-related injury }\text{participants + True }\text{Non-fall }\text{participants}}{\text{Total number of participants}}$ |  |
| --- | --- | --- |

where N_prediction of trauma_ is the number of participants for whom the machine learning model predicts the occurrence of a fall injury and who do, in fact, suffer a fall injury during the selection course; N_prediction of_ _good health_ is the number of participants for whom the model predicts the non-occurrence of a fall injury and who do not, in fact, suffer a fall injury during the selection course; and N_total_ is the total number of participants included in the study.

For the fourth secondary objective, the long-term effectiveness of the POTs intervention in preventing fall injuries between the end of the study and the end of the selection course will be evaluated using a comparative survival analysis (the Cox model). Survival curves for POTs and active control groups will be compared using the log-rank test.

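### Filling missing session questionnaires with the group mean raises the false-positive rate of the six-time awareness and stress ANOVAs in the POTs group

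*Protocol*

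**What the plan says.** The Statistical methods section of the protocol states: "Missing data will be replaced by the mean of the variable in the sample for the group under consideration (POTs or active control". It makes no exception by variable, time point or reason for absence, and the protocol names no other missing-data method and no sensitivity analysis. The same section says: "The risk of error will be set at 5%, and two-tailed tests will be used".

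Under Analysis of secondary objectives, the awareness objective is tested in the POTs group alone on "scores on the Postural Awareness Scale at the six measurement times (repeated measures ANOVA". Perceived stress is handled in the same way. Posturography and the biological stress markers are compared before and after the intervention by paired tests, also within the POTs group.

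The End-of-study visit section ends follow-up early on "the day they leave the course (for whatever reason), if this occurs before the end of the intervention". It schedules posturography, both questionnaires and saliva at that visit. The discontinuation criteria rule out re-entry. The Schedule row of the Research summary is worded differently: it places an early final visit on the day of the fall injury.

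**The concern.** A participant who leaves in the second week has a baseline score and, if the exit visit takes place, a final score, but no session scores in between. Under the rule each gap receives the average of those still attending. Every imputed value sits exactly at the mean, so it adds to the apparent sample size and nothing to the residual variation. The F-test then sees too little noise.

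Leaving is also unlikely to be unrelated to the scores. The protocol's own theory makes low awareness and high stress causes of injury, and its background data from the Marine commando course give medical unfitness as the leading cause of failure (70%). If leavers differ from stayers, replacing their scores with the stayers' mean moves the time-point means even when nobody changes.

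At stake are the questionnaire results for the first two secondary objectives, which carry the mechanistic argument. A change over time could be declared significant because of who left.

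**Working it through.** **Inputs from the protocol.** 200 participants per group; two-sided 5% level; 10% drop-out; "fall rate in the POTs group: 35" per cent; six measurement times, read from the Research summary as one initial, four follow-up and one final visit (1 + 4 + 1 = 6).

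**The plan's own figure.** For 50% against 35% at 80% power, the two-proportion formula gives 170 per group, and 170/0.9 = 189. With continuity correction it gives 183, and 183/0.9 = 204, close to the stated 200. The imputation rule does not enter this calculation, so the planned size stands.

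**Loss of spread.** If a share f of values at a time point is observed and the rest are set to the observed mean, the SD is multiplied by about √f: √0.90 = 0.95 and √0.65 = 0.81.

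**Paired test, post values missing at random.** Let both variances be σ² and the correlation ρ.

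- True variance of the mean change: (σ²/n)(1/f + 1 − 2ρ).
- Variance the test estimates after imputation: (σ²/n)(f + 1 − 2fρ).
- Ratio: 1/f, whatever ρ is.

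The actual error rate is therefore 2Φ(−1.96√f). For f = 0.90 it is 2Φ(−1.86) = 0.063. For f = 0.65 it is 2Φ(−1.58) = 0.114. These figures apply only to post values that are really absent. With exit visits complete, f = 1 and the rate is 0.05.

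**Repeated-measures ANOVA over six times, by simulation.** n = 200, no true change, 2,000 runs per scenario. Assumptions: equal correlation of 0.5 or 0.7 between times; leavers lose all later session values; imputation by the mean at that time point (the protocol does not say whether the mean is per time point). The leaving shares are the stated drop-out (10%) and the assumed POTs injury rate (35%). Ranges run over the two correlations.

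| Share leaving | At random, exit visit done | At random, exit visit missed | Leaving correlated 0.4 with own level, exit visit done |
|---|---|---|---|
| 10% | 0.070-0.081 | 0.072-0.090 | 0.120-0.198 |
| 35% | 0.163-0.188 | 0.221-0.238 | 0.624-0.870 |

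With nobody leaving, the rate was 0.044-0.058, as it should be. At 20% leaving at random with the exit visit done (correlation 0.5) it was about 0.10.

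**Does the alternative work?** A mixed model on observed values only was run 1,000 times per scenario, with correlation 0.5 and the exit visit done, beside the planned method.

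| Share leaving | Leaving | Mean imputation and ANOVA | Mixed model |
|---|---|---|---|
| 10% | random | 0.085 | 0.059 |
| 35% | random | 0.166 | 0.052 |
| 10% | related to baseline score | 0.099 | 0.050 |
| 35% | related to baseline score | 0.441 | 0.041 |

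**The case against.** The best defence is that the reach is limited, and much of it stands.

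- **Paired tests.** A reader might infer that every before-after test is inflated. The End-of-study visit section schedules the measurements on the day of leaving, so post values are not missing by design and these tests stay near 5% unless exit visits are missed.
- **Between-arm tests.** A reader might carry the inflation over to a comparison of awareness or stress between groups, using the 50% control injury rate as well. No such comparison is planned; both objectives are tested within the POTs group.
- **Injury is not leaving.** The 35% is a planning rate for fall injury; the stated drop-out is 10%. The protocol does not say how many injured participants leave. The sample codes allow for several additional visits per participant, which suggests that some continue after a fall. The 35% row is therefore a scenario.
- **Direction.** It is tempting to say that leavers would have scored worse and that the rule flatters the intervention. That is the study's hypothesis, not documented data, and people leave for any reason. The bias can go either way.
- **Primary analysis.** Taken literally, the rule would also fill in the injury outcome. That is a strained reading, because survival methods deal with leaving by censoring. The clinical covariates are few and mostly collected at one baseline visit, so gaps there should be small. No effect on the primary result has been quantified.

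Two defences do not stand. The matter cannot be treated as left to a later analysis plan, because the protocol states the rule. Nor does a sphericity correction rescue the ANOVA: with 35% leaving, Greenhouse-Geisser moved the rate only from 16% to 15.6% (random leaving) and from 62% to 61% (leaving related to level).

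**Conclusion.** The point holds for the six-time ANOVAs of postural awareness and perceived stress in the POTs group. At the protocol's own 10% drop-out the inflation is modest (about 7-8% against 5%). If every injured POTs participant left at random, it would be about 16-19%. If leaving also correlated 0.4 with the participant's level, the rates would be about 12-20% and 62-87%. These figures rest on the assumed between-visit correlations, imputation at each time point, completed exit visits and, for the last pair, the assumed 0.4.

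For the paired posturography and saliva tests the exposure depends on missed exit visits: about 6% error with 10% of post values imputed and 11% with 35%. The Cox analysis is exposed mainly through imputed baseline covariates. The rule raises the risk of a false positive; it does not show that any mechanistic result would be false.

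**What to change.** Delete the mean-replacement sentence and write in its place:

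- Awareness and stress scores are analysed by a likelihood-based mixed model on the observed values, without imputation. Alternatively, use multiple imputation with baseline value, unit, injury and time of leaving in the imputation model.
- Missing covariates in the Cox model are handled by multiple imputation.
- The injury outcome is never imputed; participants who leave without a fall injury are censored on leaving.
- A sensitivity analysis examines informative leaving. This is needed because the mixed model and multiple imputation both assume data missing at random. The simulation shows the mixed model holding its level when leaving is random or depends on the baseline score, and not beyond that.

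The Research summary and the End-of-study visit section should also be reconciled on whether the early final visit is tied to the injury or to leaving the course, since this decides how many session scores will be missing.

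The cost is one paragraph of text, slightly more analysis work and somewhat wider confidence intervals. No extra data are needed and the sample size does not change.

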**Analysis of the main objective**

The effect of the intervention (POTs *vs.* active control) on the rate of fall injuries will be evaluated using a comparative survival analysis (the Cox model, with clinical variables as potential confounders). Survival curves for POTs and active control groups will be compared using the log-rank test.

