antero-posterior

oscillations

**Figure 2 –** Biomechanical model of static postural balance, also known as the ‘inverted pendulum’ model. The body moves continuously along an antero-posterior axis and a medio-lateral axis, both originating in the medial malleoli of the ankles.

In the context of sports medicine, static postural balance is most often assessed by the Balance Error Scoring System (BESS) (Delahunt et al., 2018; Docherty, Valovich McLeod, & Shultz, 2006). This clinical test must be performed by a physician, and lasts around five minutes. In the field of cognitive neuroscience, recent work has shown the value of a paraclinical tool, posturography, to assess postural balance and investigate the individual’s level of body awareness (C. Verdonk, Trousselard, Medani, Vialatte, & Dreyfus, 2020). The analytical tools developed in the context of the latter study were subsequently used to develop another tool to assess the risk of fall injury during the STAC. Preliminary analyses show that posturography was able to correctly assess the risk of injury in 75% of trainee marine commandos (C. Verdonk et al., 2019).

The POSITION project focuses on the role of cognitive mechanisms governing body awareness as a risk factor for fall injuries during physical activities in the military. In this context, there is a clear need to evaluate the modifiability of the latter risk factor in order to develop a prevention strategy. ‘Modifiability’ means that the risk factor is amenable to an intervention that will modulate its influence on the occurrence of injury (Bahr & Holme, 2003). Specifically, the project will test the effect of *Potential Optimization Techniques* (POTs) on the cognitive mechanisms governing body awareness. We hypothesize that POTs will increase body awareness, and thus reduce the risk of fall-related injury, *via* improved postural control.

POTs were created in the 1990s by Doctor Edith Perreault-Pierre to meet needs that had never before been addressed in the armed forces: mental preparation and recovery. (Etat-major des armées - Centre national des sports de la défense, 2011). Initially developed to meet the requirements of the French Air Force regarding stress management and human factors (in the context of flight safety), they are now being deployed throughout the French Army’s other corps.

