## Study outline

In order to guarantee compliance with the experimental protocol over the two years of the study (see paragraph 3.3 for a detailed explanation), the active control intervention will be carried out in the first year (year Y), while the POTs intervention will be carried out in the second year (year Y+1).

The study will be carried out in the following six units the in the French armed forces :

1. the National Gendarmerie (Versailles-Satory, 78)
2. the 10th Air Parachute Commando (Orléans, 45)
3. the 1st Marine Infantry Parachute Regiment (Bayonne, 64)
4. the 13th Parachute Dragoon Regiment (Souge, 33)
5. the Paris Fire Brigade (Villeneuve-Saint-Georges, 94)
6. the Fusiliers Marins [Navy Riflemen] School (Lorient, 56)

The study will take place during the selection courses organized by each unit, and will last three weeks.

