## Randomization

There will be no randomization (POTs versus active control) at the individual level (i.e., for each participant in each military unit). This is not possible due to the risk of participants in the POTs group influencing those in the active control group (contamination bias). The conditions under which the selection course is carried out mean that participants in both groups are in close contact with each other. Moreover, it is possible that running the two interventions at the same time may undermine the desired team cohesion. Hence, we have chosen to carry out the study over two successive years (years Y and Y+1):

1. Participants included in year Y will follow the active control program.
2. Participants included in year Y+1 will follow the POTs program.

The order of the two interventions (active control followed by POTs) is deliberately not randomized between units, to ensure that the research protocol is respected throughout the study. If the POTs intervention was run in year Y, and was found to be beneficial, it would be very difficult to expect participating units to set up an active control in year Y+1, as it is unrealistic to expect them to abandon a program with potential benefits for candidates.

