## Data collected

### Clinical parameters

Clinical data collection will be limited to injury history, age, sex, height and weight. These data will be recorded using posturography software.

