### Para-clinical parameters

Postural balance will be measured by a clinical test (the BESS) and posturography.

1. The Balance Error Scoring System (BESS)

The BESS assesses static postural balance (eyes closed) in six conditions, using three positions (double leg stance *vs.* single leg stance *vs.* tandem stance) on two surfaces (firm *vs.* soft) (Figure 5). The participant must remain balanced without moving for 20 seconds. Points are given for postural errors (e.g., eye opening, hip flexion greater than 30°, etc.). The sum of the points obtained in the six conditions gives the total BESS score (Docherty et al., 2006)

 
[figure not shown]

**Figure 5 –** The Balance Error Scoring System is a clinical test that assesses static postural balance in six conditions, using three positions (double leg stance *vs.* single leg stance *vs.* tandem stance) on two surfaces (firm *vs.* soft).

1. Posturography

Posturography is the recording of static postural balance using a stabilometric platform (FEETEST 6^©^, Techno Concept^®^, France) (Figure 6). It consists of four small platforms that locate the position of the body’s center of pressure from the coordinates of four points of contact (left heel, left metatarsal, right heel and right metatarsal). Postural recording takes place with eyes closed, and lasts approximately one.

[figure not shown]

**Figure 6** – The FEETEST 6^©^ platform (Techno Concept^®^).

To ensure reproducibility in measurements of para-clinical parameters, investigators from the units involved in the initial assessment visit will be trained in how to carry out the BESS test (using a video). Similarly, a standard procedure will be put in place for posturography measurements.

1. Psychometric data

Self-report questionnaires will be used to measure postural awareness (the Postural Awareness Scale) and perceived stress (Cohen’s Perceived Stress Scale).

- 1. The Postural Awareness Scale (Cramer, Mehling, Saha, Dobos, & Lauche, 2018)

This questionnaire evaluates body awareness involved in postural control. A French version is currently being validated. The questionnaire is made up of 12 items, each rated from 1 (not at all true about me) to 7 (very true about me). The questionnaire assesses two dimensions of postural awareness: (*i*) Ease/Familiarity with Postural Awareness; and (*ii*) Need for Attention Regulation with Postural Awareness.

- 1. Cohen’s Perceived Stress Scale (Cohen, Kamarck, & Mermelstein, 1983)

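### The two arms are successive yearly intakes, yet the primary Cox model adjusts only for 'clinical variables', which as listed omit baseline posturography, postural awareness and perceived stress and leave the BESS unclear

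*Protocol*

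**What the plan says.** **Allocation.** Under Randomization: "There will be no randomization (POTs versus active control) at the individual level". Under Study outline, "the active control intervention will be carried out in the first year (year Y"), with POTs the year after in the same six units. Again under Randomization: "The order of the two interventions (active control followed by POTs) is deliberately not randomized between units". Arm and calendar year are therefore the same variable.

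**Primary analysis.** Analysis of the main objective gives a "comparative survival analysis (the Cox model, with clinical variables as potential confounders"), plus a log-rank comparison of the curves. The Research summary repeats the Cox wording. No other adjustment is stated.

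**Data categories.** Under Clinical parameters: "Clinical data collection will be limited to injury history, age, sex, height and weight". Under the separate heading Para-clinical parameters: "Postural balance will be measured by a clinical test (the BESS) and posturography". The same section, under a psychometric label, adds: "Self-report questionnaires will be used to measure postural awareness (the Postural Awareness Scale) and perceived stress (Cohen’s Perceived Stress Scale").

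**When measured.** The Initial evaluation visit collects the BESS, posturography, both questionnaires and saliva from every participant.

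**Role in the rationale.** The Research summary and Current knowledge sections present balance, postural awareness and stress as the hypothesised route to fall injury. They report preliminary work in which "posturography was able to correctly assess the risk of injury in 75% of trainee marine commandos". The third secondary objective is to predict injury from pre-course BESS and posturography.

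**The concern.** In a randomised trial, leaving a prognostic variable out of a Cox model costs some power and pulls the hazard ratio towards 1, but does not favour one arm. Here the arms are two intakes a year apart. A difference between intakes in a variable that predicts injury passes into the POTs hazard ratio unless the model contains that variable.

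The plan adjusts for general descriptors. Read with its own data categories, it leaves out most of the measures that the project exists to study as determinants of fall injury. The values are already in hand, so the exposure is avoidable. The unadjusted log-rank test is exposed in the same way.

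**Working it through.** **1. The plan's own figures.** Rates 50% and 35%, two-sided 5%, power 80%. The two-proportion formula with continuity correction gives 183 per group, and 183/0.90 = 204, against the stated 200. Without the correction it is 170, and 170/0.90 = 189. The stated size is reproduced to within 3% with the correction and is not in dispute.

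**2. Expected events.** 200 × 0.90 = 180 evaluable per group. Events = 180 × (0.50 + 0.35) = 153. The planned effect as a hazard ratio is ln(0.65)/ln(0.50) = 0.62.

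**3. Reading the adjustment set.**

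| Baseline measure | Where classed | In the model as written? |
|---|---|---|
| Injury history, age, sex, height, weight | Clinical parameters | Yes |
| BESS | Para-clinical heading, but called a clinical test | Unclear |
| Posturography | Para-clinical | No |
| Postural awareness, perceived stress | Psychometric | No |

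**4. Illustrative size on the rate scale.** The protocol gives no effect per SD and no year-to-year shift, so both are assumed. Take a standard normal balance score with a logistic link.

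| Event rate | Logit slope per SD | Accuracy | Change in rate, 0.2 SD | Change in rate, 0.3 SD |
|---|---|---|---|---|
| 50% | 1.0 | 0.67 | 4.1 points | 6.2 points |
| 50% | 1.5 | 0.734 | 5.3 points | 7.9 points |
| 50% | 1.8 | 0.762 | 5.8 points | 8.6 points |
| 30% | 1.15 | 0.75 | 3.8 points | 5.6 points |

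Slopes 1.5 and 1.8 bracket the cited 75% at a 50% event rate. The last row is the slope that gives 75% accuracy if only 30% are injured. The target difference is 15 points.

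**5. Illustrative size on the hazard-ratio scale.** Cox simulation with 180 per group, 2,000 runs per scenario and one normal baseline factor. The POTs intake is better by 0.2 or 0.3 SD, and POTs have no effect.

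| Assumed HR per SD of the factor | Unadjusted HR (0.2 / 0.3 SD) | False positives, unadjusted | False positives, adjusted |
|---|---|---|---|
| 1.25 | 0.96 / 0.93 | 5.6% / 6.9% | 4.6% / 4.8% |
| 1.5 | 0.93 / 0.89 | 7.4% / 11.4% | 4.5% / 4.6% |
| 2.0 | 0.89 / 0.83 | 13.8% / 22.5% | 4.3% / 5.1% |

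The adjusted hazard ratio averages 1.00 throughout. With a true ratio of 0.62, the unadjusted estimate falls to between 0.60 and 0.54 under the same shifts, while the adjusted one stays at 0.62.

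With no shift and a true ratio of 0.62, adjustment changes power from 83% to 85% at HR 1.25 per SD, and from 77% to 86% at HR 2.0 per SD.

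**6. Can the sample carry it?** Treatment plus five clinical variables is 6 terms: 153/6 = 25.5 events per term. Adding BESS, one posturography summary, awareness and stress gives 10 terms: 153/10 = 15.3. If both awareness dimensions enter, 11 terms: 153/11 = 13.9. Stratifying by unit spends no coefficients; five unit indicators instead would give 16 terms and 9.6 events per term.

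**The case against.** **The term is loose, and covariate lists often sit in a statistical analysis plan.** The analysis section does not point to the Clinical parameters section, and the Initial evaluation visit gives a slightly different list of clinical data, without injury history. This is fair, and it is why the point is worded as a reading. But the protocol does fix a category of confounder, and nowhere does it place posturography, awareness or stress in that category.

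**A reader might infer that all balance measures are excluded.** The documents do not support that for the BESS, which the Secondary objectives and Para-clinical parameters sections call a clinical test. Its status is unclear.

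**A reader might infer that the protocol regards these as the main established risk factors.** It does not. Its language is conditional throughout, and it also names age, gender, physical condition and tobacco as intrinsic factors.

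**The size rests on assumptions.** This stands. The 75% is preliminary, from marine commando trainees, with no event rate or validation given. No passage supports a 0.2 or 0.3 SD drift. Sampling alone gives an SE of √(2/200) = 0.10 SD for the intake difference, but a randomised trial has that too, so it is no evidence of drift. A weak factor (HR 1.25 per SD) gives little bias. One posturography summary may carry less than the full analytical tool behind the 75%.

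**Baseline may not be baseline.** This stands. The intervention section places the first two sessions ideally on the day before the course. The Study visit schedule puts the briefing on that day, and the inclusion and initial visits follow a day later. Values taken after a session could already reflect the intervention, and adjusting for them could remove part of its effect.

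**Conclusion.** The point holds as a correctable weakness in the primary analysis. Read with the protocol's data categories, the model omits three baseline measures on the hypothesised causal pathway and leaves a fourth, the BESS, undetermined, in a comparison where arm equals year.

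The size is illustrative only: about 5 to 6 points of injury rate for a 0.2 SD intake difference with a strong predictor, about 4 points with a weaker one, and a false-positive rate from barely above 5% up to about 23% across the simulated range. The direction of any bias is unknown. The simulated shift favours POTs by construction; a shift the other way would hide a benefit.

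It would be wrong to infer that the result is already known to be biased, or that wider adjustment makes the comparison equivalent to a randomised one. Weather, course content and injury recording in a given year cannot be separated from arm by any covariate.

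**What to change.** - Name the primary adjustment set: injury history, age, sex, height, weight, baseline BESS total, one pre-specified posturography summary, baseline Postural Awareness Scale and baseline Perceived Stress score, stratified by unit. State whether the awareness scale enters as one score or as its two dimensions.
- Make this adjusted model the primary inference and label the unadjusted log-rank test descriptive.
- Use only values measured before session 1, and reconcile the session timing in the intervention section with the briefing and inclusion timing in the visit schedule so that such values exist for everyone.
- Do not add prior POTs hours unless they are actually recorded. The protocol uses a 10-hour threshold for exclusion but lists no hours among the data collected.
- Check how the planned group-mean replacement of missing values would act on these covariates, since it would weaken the adjustment.
- State that calendar-year effects remain confounded with arm, as a limit on the conclusion.

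**Cost.** Wording, the choice of one posturography summary, and four or five more model terms, at about 14 to 15 events per term. No new data are needed, provided the baseline timing is settled.

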# EVALUATION CRITERIA

## Primary endpoint

The primary endpoint will be the rate of fall injuries following a loss of balance in each of the two groups (POTs *vs.* active control).

A fall injury will be recorded by the medic responsible for providing healthcare during the selection course. The injured participant will be required to attend an additional follow-up visit on the same day after the initial medical consultation.

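### An unadjusted log-rank test sits beside the adjusted Cox model for the non-randomised primary comparison, and the protocol does not say that it has no bearing on the conclusion

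*Protocol*

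**What the plan says.** For the primary comparison, the Protocol's section Analysis of the main objective gives a "comparative survival analysis (the Cox model, with clinical variables as potential confounders". Its next sentence reads: "Survival curves for POTs and active control groups will be compared using the log-rank test". No stratification or adjustment of the log-rank test is mentioned.

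The general rule under Statistical methods is: "The risk of error will be set at 5%, and two-tailed tests will be used". The Research summary (row Statistical analysis) names the Cox model for the primary objective and does not mention the log-rank test. No section calls either test primary, supportive or descriptive.

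On allocation, the section Randomization says: "There will be no randomization (POTs versus active control) at the individual level". It adds: "The order of the two interventions (active control followed by POTs) is deliberately not randomized between units". Active control therefore runs in year Y and POTs in year Y+1 in every unit. The section Clinical parameters states: "Clinical data collection will be limited to injury history, age, sex, height and weight".

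The Cox and log-rank pair returns for the fourth secondary objective, under Analysis of secondary objectives. There the Cox model is given without covariates.

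**The concern.** In a randomised trial, a log-rank test beside an adjusted Cox model does little harm, because both tests are valid when there is no treatment effect. Here the groups are two intakes a year apart, and the protocol itself allows that clinical variables may confound the comparison. The Cox model takes those variables into account; a plain log-rank test does not.

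If the intakes differ, on balance, on variables that predict injury, the log-rank test attributes the difference to POTs or lets it hide a POTs effect. The two p-values can then fall on opposite sides of 5%. The protocol implies which one leads but does not say what weight the other carries. At stake is whether a significant log-rank result, with a non-significant adjusted result beside it, could be presented as the primary finding, or the reverse.

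**Working it through.** **1. The plan's own figure.** Calculating the number of subjects required gives 50% v 35%, two-tailed 0.05, power 0.80, 10% drop-out and 200 per group. For two proportions:

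n = [1.96·√(2·0.425·0.575) + 0.842·√(0.25 + 0.2275)]² / 0.15² = 170 per group.

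The continuity correction raises this to 183. Allowing for 10% drop-out gives 183/0.90 = 204 or 183 × 1.10 = 202, so 200 is reproduced to within 3%. Without the correction the figure is 170/0.90 = 189. The calculation compares two proportions and is specific to neither the Cox model nor the log-rank test.

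**2. What the protocol does not supply.** It gives neither the prognostic strength of the clinical variables nor the size of any difference between intakes. Both are assumptions below, shown as a range.

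**3. Hand approximation, no POTs effect.** Take 180 analysed per group, 50% injured and about 10% leaving early. That gives about 170 events and a standard error of the log hazard ratio of about 2/√170 = 0.153. A covariate with hazard ratio 1.5 per SD and a 0.3 SD shift biases the unadjusted log hazard ratio by ln(1.5) × 0.3 = 0.405 × 0.3 = 0.12, or 0.12/0.153 = 0.79 standard errors. Then P(|Z + 0.79| > 1.96) is about 12%.

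**4. Simulation, no POTs effect, intakes differing.** Exponential times, 3 weeks of follow-up, log-rank test v Wald test of the group coefficient in the adjusted Cox model:

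| Covariate effect per SD | Shift | Log-rank rejects | Cox rejects | Tests disagree |
|---|---|---|---|---|
| HR 1.5 | 0.3 SD | 12% to 12.5% | 4% to 6% | 10% to 12% |
| log-HR 0.5 | 0.2 SD | about 10% | about 5% | about 9% |
| log-HR 0.5 | 0.4 SD | about 26% | about 5% | about 26% |
| HR 2.0 | 0.3 SD | 22% | 5% | 22% |

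The first row agrees with step 3.

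**5. Simulation, no POTs effect, balanced intakes.** If significance on either test counted, the rejection rate would be 5.6%, 6.9%, 7.6% and 9.0% at log-HR 0, 0.3, 0.5 and 0.8 per SD. The Monte Carlo standard error is about √(0.05 × 0.95/2000) = 0.5 points. Over hazard ratios up to about 2.0 per SD this is roughly 6% to 8%. Two independent tests would give 1 − 0.95² = 9.75%, but the two statistics correlate at 0.84 to 0.998.

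**6. Planned effect.** Under proportional hazards the hazard ratio is ln 0.65 / ln 0.50 = 0.62. With an HR 1.5 covariate and a 0.2 SD shift against POTs, log-rank power is 64% to 66% and Cox power 83%. With log-HR 0.5 and a shift against POTs, the tests disagree in 22% (0.2 SD) to 45% (0.4 SD) of trials. With a shift in favour of POTs they disagree in 9% to 15%.

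**7. Does relying on Cox alone need a larger trial?** Expected events are 180 × (0.50 + 0.35) = 153 with 180 evaluable per group, or 200 × 0.85 = 170 with all 200. Schoenfeld's formula gives power Φ(√153 × 0.476/2 − 1.96) = 83.7%, and 87.3% with 170 events. Simulated Cox power with 200 per group is 83% to 88%. Sample size and alpha can stay.

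**The case against.** The strongest reply is that the text already points to the Cox model. The main-objective section assigns the effect of the intervention to it, the log-rank sentence concerns the curves and is a routine companion to them, and the summary names Cox alone. That stands. A reader might infer that the summary and the methods section contradict each other; they do not, since the summary is only shorter.

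A second reply is that labelling tests as confirmatory or supportive is commonly left to an SAP, which may exist. That also has force: a missing label alone would be no finding. What remains is that the protocol itself names, for its main objective, an unadjusted test that does not suit a non-randomised comparison, without limiting its role.

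Three stronger readings are not supported:

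- A reader might infer that significance on either test would count as success, so that the stated 5% is breached. No such rule appears, and with balanced intakes the inflation would be modest.
- A reader might infer that the log-rank test fails whenever the intakes differ on any clinical variable. It is biased only by a net difference on variables that predict injury. A difference on a non-prognostic variable does no harm, and several differences can offset each other. The protocol speaks only of potential confounders and gives no evidence that an imbalance will occur.
- A reader might infer that the adjusted Cox model removes the confounding. It addresses measured variables only. Year is fully confounded with group and affects both tests. The simulations also favour Cox, because their confounder is measured and correctly modelled.

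**Conclusion.** The point holds in limited form. The primary contrast between successive intakes is analysed by an adjusted Cox model, which the text implies is the lead analysis, and by a plain log-rank test whose role is not limited.

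The problem is mainly confounding rather than multiplicity. Under an assumed hazard ratio of 1.5 to 2.0 per SD and a 0.3 SD shift, the log-rank test rejects in about 12% to 22% of null trials against about 5% for Cox. With balanced intakes the cost is about 6% to 8% instead of 5%, and only under an either-test reading that the protocol does not state. The larger figures depend on covariate strengths and shifts that the protocol does not give, so they show what could happen rather than what to expect.

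**What to change.** In Analysis of the main objective and in the summary's Statistical analysis row, state that the primary conclusion rests on the two-sided 5% test of the group coefficient in the adjusted Cox model, reported with its 95% confidence interval. Keep the survival curves as description, and label the log-rank p-value unadjusted and supportive.

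For the fourth secondary objective, make the same adjusted Cox model the deciding analysis, with the clinical variables already collected (injury history, age, sex, height and weight), and give the log-rank test the same supportive label. Naming these variables for the primary model as well would matter, since without a fixed list the Cox result is not unique either.

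State in the same place that adjustment covers measured variables only, and that the difference between the two calendar years cannot be separated from the intervention.

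The cost is a few sentences, with no new data and no change to sample size or alpha. The one downside is that a significant log-rank result alone can no longer be presented as the primary result.
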